**Figure 4 figure4:**
[figure not shown]
Bioinformatics pathway analysis to identify any key genes and proteins involved in the association between polycystic ovary syndrome (PCOS) and endometrial cancer (EC).

**Table 1 table1:** Experimental plate design for cell culture studies.

Plates											
1	2	3	4	5	6	7	8	9	10	11	12
PCOS^a^ 1	PCOS 1 + IGF^b^	PCOS 1 + Inhibitor	PCOS 1 + IGF + Inhibitor	PCOS 2	PCOS 2 + IGF	PCOS 2 + Inhibitor	PCOS 2 + IGF + Inhibitor	PCOS 3	PCOS 3 + IGF	PCOS 3 + Inhibitor	PCOS 3 + IGF + Inhibitor
PCOS 1	PCOS 1 + IGF	PCOS 1 + Inhibitor	PCOS 1 + IGF + Inhibitor	PCOS 2	PCOS 2 + IGF	PCOS 2 + Inhibitor	PCOS 2 + IGF + Inhibitor	PCOS 3	PCOS 3 + IGF	PCOS 3 + Inhibitor	PCOS 3 + IGF + Inhibitor
PCOS 1	PCOS 1 + IGF	PCOS 1 + Inhibitor	PCOS 1 + IGF + Inhibitor	PCOS 2	PCOS 2 + IGF	PCOS 2 + Inhibitor	PCOS 2 + IGF + Inhibitor	PCOS 3	PCOS 3 + IGF	PCOS 3 + Inhibitor	PCOS 3 + IGF + Inhibitor
PCOS 1	PCOS 1 + IGF	PCOS 1 + Inhibitor	PCOS 1 + IGF + Inhibitor	PCOS 2	PCOS 2 + IGF	PCOS 2 + Inhibitor	PCOS 2 + IGF + Inhibitor	PCOS 3	PCOS 3 + IGF	PCOS 3 + Inhibitor	PCOS 3 + IGF + Inhibitor
Control 1	Control 1 + IGF	Control 1 + Inhibitor	Control 1 + IGF + Inhibitor	Control 2	Control 2 + IGF	Control 2 + Inhibitor	Control 2 + IGF + Inhibitor	Media (FBS^c^)	Media (FBS) + IGF	Media (FBS) + Inhibitor	Media (FBS) + IGF + Inhibitor
Control 1	Control 1 + IGF	Control 1 + Inhibitor	Control 1 + IGF + Inhibitor	Control 2	Control 2 + IGF	Control 2 + Inhibitor	Control 2 + IGF + Inhibitor	Media (FBS)	Media (FBS) + IGF	Media (FBS) + Inhibitor	Media (FBS) + IGF + Inhibitor
Control 1	Control 1 + IGF	Control 1 + Inhibitor	Control 1 + IGF + Inhibitor	Control 2	Control 2 + IGF	Control 2 + Inhibitor	Control 2 + IGF + Inhibitor	Media (FBS)	Media (FBS) + IGF	Media (FBS) + Inhibitor	Media (FBS) + IGF + Inhibitor
Control 1	Control 1 + IGF	Control 1 + Inhibitor	Control 1 + IGF + Inhibitor	Control 2	Control 2 + IGF	Control 2 + Inhibitor	Control 2 + IGF + Inhibitor	Media (FBS)	Media (FBS) + IGF	Media (FBS) + Inhibitor	Media (FBS) + IGF + Inhibitor

^a^PCOS: polycystic ovary syndrome.

^b^IGF: insulin-like growth.

^c^FBS: fetal bovine serum.

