The primary outcome measure will be the difference in cell proliferation measured by cell index values during the xCELLigence real-time cell proliferation experiment. Comparison of cell index values from cells treated in different groups will be performed by the Kruskal-Wallis test followed by multiple comparison tests.

### Objective 2: Identifying Differentially Expressed Genes and Pathways Activated by the Treatment of Endometrial Cell Lines of the Different Study Groups Listed in Objective 1

We will perform transcriptomic profiling of endometrial cell lines to identify differentially expressed genes in response to different study conditions outlined previously, using RNA Sequencing (RNA-Seq) to identify the molecular targets and pathways involved in the oncogenic effects (Figure 3).

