Although the study will aim to recruit 20 women with PCOS and 20 women without PCOS aged between 18 and 45 years, we will begin with a pilot study of samples from 3 women with PCOS and 2 controls and perform validation studies in the larger cohort of 20 women with PCOS and 20 women. The experimental plate design for the cell-culture studies in this feasibility study is illustrated in Table 1.

It will be 1 plate per cell line for each time point (24 h and 48 h). All experiments will be conducted in quadruplicates. We recognize that opinions differ about the ideal sample size for cell-culture experiments [28]; however, we believe our proposed experiments are stringent enough to make the results believable.

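### The pilot plate map puts every PCOS well in the top half and every control-serum well in the bottom half, so serum group cannot be separated from plate position

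*Protocol article*

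**What the plan says.** The map is Table 1 of the Protocol article, titled "Experimental plate design for cell culture studies". The last paragraphs of Methods, Objective 3: Bioinformatics, say where it applies. Work starts with a "pilot study of samples from 3 women with PCOS and 2 controls", and "The experimental plate design for the cell-culture studies in this feasibility study is illustrated in Table 1". They also set the number of plates, "It will be 1 plate per cell line for each time point (24 h and 48 h"), and the replication: "All experiments will be conducted in quadruplicates".

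The table body has 8 rows and 12 columns. Rows 1-4 hold only PCOS 1, 2 and 3. Rows 5-8 hold only Control 1 and 2 (columns 1-8) and media (columns 9-12). Within each serum the additives always run in the same left-to-right order: alone, IGF, inhibitor, both. Each condition, for example "Control 1 + IGF + Inhibitor", occupies four stacked wells of one column.

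On the outcome, the section Endometrial Carcinoma Cell Lines says: "The primary outcome measure will be the difference in cell proliferation measured by cell index values". On the analysis it says: "Comparison of cell index values from cells treated in different groups will be performed by the Kruskal-Wallis test followed by multiple comparison tests". The article states no rotation or randomisation of wells, no exclusion of edge wells and no adjustment for position.

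**The concern.** Readings from a multiwell plate can depend on where the well is, through seeding order, dispensing, temperature or evaporation at the rim. A layout guards against this by spreading the compared conditions over positions. Table 1 does the opposite for the main contrast, because it gives each serum group its own half of the plate. A row effect would then look exactly like a PCOS effect.

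Quadruplicate wells do not help. The four replicates of a condition share a column and a plate half, so they repeat the position effect and do not average it out. If the four plates (2 cell lines × 2 time points) all follow Table 1, agreement between them would not rule out an artefact of position either.

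The additive contrasts bear on whether IGF-1 mediates the effect. They are balanced over rows but not over edge wells.

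**Working it through.** **Inputs.** The well positions come from Table 1. The plate count comes from Methods, Objective 3. The size of any row or edge effect is not in the article, so it is kept as a symbol.

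**1. Reproduce the layout.** There are 6 sera or media (PCOS 1-3, Control 1-2, media) and 4 additive states, which gives 24 conditions. 24 × 4 replicates = 96 wells = 8 × 12. This agrees with the quadruplicates stated.

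**2. Serum group against plate half.**
- PCOS: 48 of 48 wells in rows 1-4, mean row (1+2+3+4)/4 = 2.5.
- Control serum: 32 of 32 wells in rows 5-8, mean row (5+6+7+8)/4 = 6.5.
- A model with intercept, serum group and plate half has rank 2 of 3. Group and half are the same variable on these plates.
- A step of size h between the halves enters PCOS versus control in full.
- A linear drift of total size D from row 1 to row 8 (7 steps) enters as (6.5 − 2.5)/7 × D = 4/7 D, or 57% of D.

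**3. Edge exposure.** Edge means row 1, row 8, column 1 or column 12, which is 36 of 96 wells (37.5%).

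| | Alone | IGF | Inhibitor | IGF + inhibitor |
|---|---|---|---|---|
| PCOS serum | 6/12 | 3/12 | 3/12 | 6/12 |
| Control serum | 5/8 | 2/8 | 2/8 | 2/8 |
| Media | 1/4 | 1/4 | 1/4 | 4/4 |
| All | 12/24 | 6/24 | 6/24 | 12/24 |

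Let e be the difference between edge and interior wells. The bias in alone versus IGF, or alone versus inhibitor, is the difference in edge share times e:
- PCOS serum: (6/12 − 3/12)e = 0.25e.
- Control serum: (5/8 − 2/8)e = 0.375e.
- The difference between these two contrasts, which asks whether the additive effect differs by serum group: (0.375 − 0.25)e = 0.125e.

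Edge share hardly touches the overall group contrast: PCOS 18/48 (37.5%) against control serum 11/32 (34.4%). The threat to PCOS versus control is plate half. The edge imbalance mainly affects the additive contrasts.

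**4. Can the same wells do better?** One two-row block has 2 × 12 = 24 wells, exactly the 24 conditions. Four such blocks fill the plate, each holding every condition once in random order. Over 2,000 simulated layouts of this kind:

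| | Table 1 | Randomised blocks, mean (SD) |
|---|---|---|
| Mean row, PCOS minus control | −4.0 | 0.00 (0.12) |
| Edge share, alone minus IGF | +0.25 | 0.00 (0.13) |
| Rank, group and half | 2 of 3 | 3 of 3 (in the 50 layouts checked) |

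The SD of 0.13 shows that a single random map can still be somewhat unbalanced at the edge. This is why each plate needs its own randomisation.

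**The case against.** The strongest reply is scope. The map is stated for the feasibility study only, and the Discussion (Expected Outcomes) says that the pilot is there to find methodological problems before the larger cohort is studied. With women as units, 3 against 2 gives C(5,2) = 10 arrangements, so the smallest two-sided exact rank p-value is 2/10 = 0.20. The pilot could not settle PCOS versus control even on a perfect plate.

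That limits the consequence but does not remove the point. A pilot meant to expose methodological problems cannot expose a row effect if its map makes that effect look like a PCOS effect.

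A reader might infer more than the article supports:
- **That the map will be reused for 20 + 20 women.** The article gives no map for that cohort, so counts of plates needed under reuse would criticise a plan that is not there.
- **That the results will be biased by some percentage.** No edge or row effect is quantified. What is shown is confounding by design.
- **That baseline wells alone are over-exposed at the edge.** IGF + inhibitor wells are equally exposed overall (12/24) and within PCOS serum (6/12). Baseline media wells are not over-exposed (1/4). Only in control serum does baseline stand alone. Nor do all baseline wells sit in column 1: they are in columns 1, 5 and 9.

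Some ambiguity also stands. The table's header row is labelled as plates, not columns. The 8 × 12 body and the rule of one plate per cell line and time point make a 96-well map the likely reading. The table does not name the assay, so it is an inference that the cell index wells follow it.

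**Conclusion.** The point holds for the pilot map. Serum group and plate half are completely aliased, and no analysis of plates laid out this way can separate them. All of a half-plate step, or 57% of a linear row drift, would be read as PCOS versus control. Alone versus a single additive carries 0.25e in PCOS serum and 0.375e in control serum.

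This rests on reading Table 1 as a physical 96-well map, on that map being used for the cell index wells, and on the same map serving each of the four plates, since no other is described. The sizes of h, D and e are unknown and could be small.

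The layout is printed in the article, so this is not a detail left to a fuller document. It is a moderate, cheaply removed design weakness, and it would become serious only if the layout were carried into the 20 + 20 cohort.

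**What to change.** Replace Table 1 with a randomised block map on the same 96 wells: four two-row blocks, each holding all 24 conditions once in random order. Draw a new randomisation for each plate. State that the Table 1 layout will not be used for the 20 + 20 cohort, and that both serum groups will be on every plate there.

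The Results section says that data collection has begun and that the 3 + 2 women are recruited, so pilot plates may already have been run. If so, report the pilot's PCOS-control differences as inseparable from plate half, and apply the new map from the next plate on.

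No extra wells or sera are needed. The cost is more complex dispensing and a somewhat higher risk of misplaced wells, which a printed map for each plate can control.

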## Results

In this study, we have described the protocol for an ongoing study to investigate the role of IGF-1 in mediating the risk of EC in women with PCOS. The study will aim to recruit 20 women with PCOS and 20 controls and measure the effect of serum from these women on cell proliferation and molecular pathways in human EC cell lines, compared with IGF-1 and IGF-1 antagonists. Recruitment for the study is currently ongoing. The project was funded in June 2022 and approved by the Mohammed Bin Rashid University of Medicine and Health Sciences’ IRB in October 2022; funds were released in January 2023, and data collection began on 16 March 2023 and is ongoing. Three women with PCOS and 2 controls have been recruited as the date of this submission from 1 hospital site and IRB permission for further participant recruitment at a second hospital site was granted in October 2023. Data analysis has not yet commenced. We anticipate that initial results for analysis and publication will be available by the summer of 2024.

## Discussion

### Expected Outcomes

Although the protocol (using cell culture) described in this paper is not novel for studying molecular mechanisms to help in the prevention and treatment of diseases, the unique aspect of it is that no previous study has used this approach to investigate the oncogenic effect of serum from women with PCOS. More importantly, no previous study has considered the differential mutations of genes related to the insulin signaling pathway in human endometrial cell lines and the potential impact this may have on their experimental findings.

A possible limitation of our protocol includes the risk that the IGF-1 present in the serum of women with PCOS may become diluted in the cell culture media to an extent where the in vitro effects do not represent the in vivo activity. We will, however, aim to mitigate this risk by using Sep-Pak C18 for the extraction, concentration, and fractionation of peptides from PCOS and control serums [29]. We will also begin with a pilot study of samples from 3 women with PCOS and 2 controls to identify any other potential methodological problems before performing validation studies in the larger cohort of 20 women with PCOS and 20 women without PCOS. Another limitation of our protocol is that the use of these cell lines may limit the generalizability of the findings from our study. However, our results may inform future studies by independent research groups using primary cell lines or patient tumor samples.

### Conclusions

In conclusion, this study describes a protocol for an ongoing study to investigate the role of IGF-1 in mediating the risk of EC in women with PCOS, by investigating the effect of serum from women with PCOS and controls on cell proliferation and molecular pathways in human EC cell lines. Although we currently do not have any results to report, reporting our protocol should aid research collaboration and early feedback; it could also reduce duplication of effort by other research groups. The broader implications of the findings of our study, when available, are that a deeper understanding of the mechanisms underlying the regulation of the IGF system in PCOS and EC will improve our ability to develop effective treatment modalities for EC. Specifically, investigating how IGF-1 in PCOS participates in the development of EC may identify novel genetic associations between EC and PCOS. This will also facilitate future systems biology–based pathway analysis to explore further molecular mechanisms leading to EC and will be a vital step in reducing EC in women globally.

## Abbreviations

AKT: protein kinase B
EC: endometrial cancer
ERK: extracellular signal-regulated kinase
HEC: human endometrial cancer
IGF-1: insulin-like growth factor 1
IRB: Institutional Review Board
PCOS: polycystic ovary syndrome
PI3K: phosphoinositide 3-kinase
RNA-Seq: RNA sequencing
